### B. Study Populations

The study populations are sex workers, MSM and transgender women, at least 15 years of age who are residents of a to-be-defined geographic area at time of interview. International definitions of key populations follow:

- Sex worker (from the UNAIDS Guidance Note on HIV and Sex Work): “female, male and transgender adults and young people who receive money or goods in exchange for sexual services, either regularly or occasionally”. This definition includes those who occasionally exchange sex for gifts. It does not include people younger than 18.
- Men who have sex with men: MSM is an abbreviation used for ‘men who have sex with men’ or ‘males who have sex with males’. The term ‘men who have sex with men’ describes males who have sex with

males, regardless of whether or not they have sex with women or have a personal or social gay or bisexual identity. This concept is useful because it also includes men who self-identify as heterosexual but have sex with other men. However, abbreviations should be avoided whenever possible. Writing out the term is preferred.

- Transgender persons: ‘individuals whose gender identity and/or expression of their gender differs from social norms related to their gender of birth. The term transgender persons describes a wide range of identities, roles and experiences which can vary considerably from one culture to another.’

Operational population definitions and inclusion criteria will be established either through the mapping readiness assessment or during data analysis based on participants’ responses to the behavioral questionnaire.

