#### *Inclusion Criteria for PLACE*

Male and female participants who meet the following eligibility criteria will be invited to participate in the project:

- At least 15 years of age at time of interview and not accompanying or running an errand for parents
- Recruited at selected venues
- Consent to participant in a face-to-face structured behavioral survey and provide written informed consent with initials or an X

Additionally participants that meet one of the following inclusion criteria for key populations will be offered additional STI testing:

- At least one sexual contact for cash in the last 12 months
- Man or transgender woman that has had oral or anal sex with another man in the past 12 months
- Identification as a male-to-female transgender woman

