|--------------|-----------------------------------------------------------------------------------------------------|------------------|--------------------------------------------------------------------------------------------------------------------------------------------------------------------------------------------------------------------------------------------------------|
|              | Percentage of men reporting the use of a condom the last time they had anal sex with a male partner | 1.12; O-4e, O-4g | 
Num: Number of male or transgender respondents who report condom use at last anal sex with a male partner in the last 12 months.
 
Denom: Number of male respondents who have had sex with at least one male partner in the past 6 months.
 |
| Stigma       | Percentage of key populations reporting stigma and discrimination                                   | O-5a             | 
Num: Number of people who report experiencing stigma or discrimination due to their sexual orientation, work or HIV status
 
Denom: Number of people interviewed
                                                                           |
|              | Percentage of people from key populations who have experienced discrimination by health workers     | NEEDS.7          | 
Num: Number of people who report experiencing discrimination by a health care worker
 
Denom: Number of people interviewed
                                                                                                                 |

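### Protocol VI.B lets key-population definitions be set during data analysis, in conflict with criteria fixed elsewhere; one Table 4 MSM indicator also has a mismatched numerator and denominator

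*Protocol*

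**What the plan says.** Section VI.B (Study Populations) first gives international background definitions. The one for sex workers covers people "who receive money or goods in exchange for sexual services, either regularly or occasionally" and adds: "This definition includes those who occasionally exchange sex for gifts". It carries no recall window. The section closes by saying "Operational population definitions and inclusion criteria will be established either through the mapping readiness assessment or during data analysis", and the rest of that sentence ties this to participants' questionnaire responses.

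Other sections state criteria outright:

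- Inclusion Criteria for PLACE lists three for key populations. The sex-work criterion is "At least one sexual contact for cash in the last 12 months". The criterion on sex with a man is "Man or transgender woman that has had oral or anal sex with another man in the past 12 months". The third is "Identification as a male-to-female transgender woman". Their stated use there is to decide who gets extra tests: "Additionally participants that meet one of the following inclusion criteria for key populations will be offered additional STI testing".
- Risk assessment and collection of biologic specimens applies much the same rule in the field.
- The RDS inclusion criteria for Cabinda require cash for sex within 12 months, age 15 or over, residence, a valid coupon and consent.

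In Table 4, the indicator on condom use at last anal sex between men has the denominator "Number of male respondents who have had sex with at least one male partner in the past 6 months". Its numerator covers male or transgender respondents over 12 months.

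**The concern.** VI.B offers two moments for fixing who counts as a sex worker, an MSM or a transgender woman. One comes before fieldwork. The other comes after the questionnaire answers and HIV results are in the database. No rule, deadline or order of precedence is attached. Since the criteria are already written down elsewhere, the protocol contradicts itself on when they are fixed.

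This is more than a detail left to an analysis plan. The protocol positively permits late definition, and a separate plan would not remove that text. At stake are the estimates reported by key population, and comparability between provinces if different rules were applied in each.

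The Table 4 indicator is a separate fault. People can enter its numerator without being in its denominator, so it is not a proportion as written.

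**Working it through.** The protocol gives no figure on this point to reproduce. The check is to set the texts side by side and ask which estimates a late choice could move.

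**1. Where membership is open**

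- Step 4 says people approached at random at venues are not screened on sex work or same-sex practices. All participants are HIV tested. Membership at venues is therefore assigned from answers after enrolment and testing.
- Form C holds more than one usable rule. C11 asks about money for sex in the past 12 months and C12 asks about ever. For MSM, C10 asks about anal sex with a man in 12 months and C6 counts male partners in 4 weeks.
- HIV prevalence (people tested), cascade steps (people with HIV) and coverage (people interviewed) are reported by population, so each depends on the rule chosen.

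**2. Where membership is not open**

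- Cabinda: the sex-work criterion is applied at entry.
- STI prevalence: denominators are people tested, and tests are offered in the field on the stated criteria. The group could be narrowed later but not widened.
- Condom use with last client: the Table 4 denominator states its own 12-month window.

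**3. Whether the stated criteria can be applied with Form C**

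- Cash for sex, 12 months: C11 fits.
- Transgender identity: Q14 (sex at birth) and Q15 (current identification) fit. The criterion has no time window.
- Oral or anal sex with a man, 12 months: C10 asks about anal sex only, so the criterion cannot be fully derived.
- Sex for goods: Form C has no such item for the respondent.

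**4. The Table 4 MSM condom indicator**

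| | Who | Window | Act |
|---|---|---|---|
| Numerator | male or transgender | 12 months | last anal sex with a male partner |
| Denominator | male | 6 months | sex with a male partner |

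The two differ in all three respects, and Form C has no 6-month item.

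**5. Illustration of size (assumptions, not protocol results)**

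Inputs: 600 sex workers and about 600 others in Luanda (VI.E); 8.5% HIV prevalence among women in transactional sex in Cunene and 2.4% among adults nationally (Background). Let s be the assumed share of the 600 others whom a wider rule would count as sex workers.

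Prevalence = (600 × 0.085 + 600 × s × 0.024) / (600 + 600 × s)

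- s = 5%: 51.72/630 = 8.2%
- s = 10%: 52.44/660 = 7.9%
- s = 25%: 54.60/750 = 7.3%
- s = 50%: 58.20/900 = 6.5%

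The shift is 0.3 to 2.0 points. The 95% half-width at n = 600, treated as a simple random sample, is 1.96 × √(0.085 × 0.915/600) = 2.2 points, before any design effect. The shift is inside sampling error, but it is systematic.

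The example assumes that reclassified people carry the national adult prevalence. If past sellers of sex had a prevalence nearer 8.5% the shift would shrink, and above 8.5% it would reverse. It also assumes C11 and C12 are put to everyone, whereas the Section C heading in Form C tells the interviewer to continue only with key-population members.

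**The case against.** The best defence is that the disputed sentence describes ordinary practice. It goes on to say that definitions rest on questionnaire responses, people approached at random at venues are not screened on behaviour, and Table 1 speaks of populations defined in the questionnaire. On that reading it means only that individuals are classified from their answers. That stands as far as the use of responses goes. It does not cover timing: the sentence says that the definitions and inclusion criteria themselves, not just the classification of individuals, may be established at analysis.

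Several stronger readings are tempting, and the documents do not support them:

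- A reader might infer that every denominator is open. Cabinda entry, the STI denominators and the condom-with-client indicator show otherwise.
- A reader might infer that VI.B overrides the stated criteria. No text ranks one above the other; precedence is simply unstated.
- A reader might count money-or-goods as a rival operational definition. It is quoted as international background, and Form C could not apply it to venue participants.
- A reader might take the 6-month window as a rival definition of MSM. It belongs to one indicator and is an internal mismatch.
- A reader might expect sex-worker prevalence to rise under a narrower recency rule. For paid sex Form C records only 12 months, ever and age at first sale, so a narrower paid-sex window cannot be formed.
- A reader might call the estimates biased. A different definition changes the quantity estimated; bias requires selective choice, which the text permits but does not prescribe.

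**Conclusion.** The point holds in limited form. VI.B conflicts with the PLACE, specimen-collection and Cabinda criteria on when population definitions are fixed. The practical exposure is venue-based HIV prevalence, cascade and coverage by population. The documents do not determine its size: the 0.3 to 2.0 point shift is an illustration of a wider sex-work rule and depends on the assumed share and prevalence. An unseen analysis plan may already fix the definitions, which would reduce the risk but leave the contradiction in the protocol.

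The Table 4 MSM condom indicator is wrong as written. That conclusion needs no assumption.

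Both should be corrected. Neither threatens the study's design.

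**What to change.** 1. In VI.B, delete the option of establishing definitions and inclusion criteria during data analysis. Say instead that individuals are classified from their responses using criteria fixed beforehand. Any change arising from the mapping readiness assessment should be recorded before fieldwork.
2. Name those criteria. For venues, use the PLACE list: cash for sex in 12 months; sex with a man in 12 months; transgender identity with no time window. For Cabinda, use the RDS inclusion criteria. Do not impose the PLACE list on every Table 4 denominator, since many are people diagnosed with HIV, viral load tests or ART start-up groups.
3. Before fieldwork, tie each criterion to a named item, for example C11 for cash and Q14 with Q15 for transgender identity. Reconcile the oral-or-anal criterion with C10. Make clear that the items establishing membership are asked of everyone, despite the Section C heading.
4. Change the Table 4 MSM condom denominator to male or transgender respondents who had anal sex with a male partner in the past 12 months, matching its numerator.
5. Label results under any other definition as sensitivity analyses.

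Cost: wording, plus a small Form C edit if oral sex stays in the criterion. No change to sample size or sampling.

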### **C. PLACE-Programmatic Mapping Survey Procedures**

PLACE is a cross-sectional study. The general PLACE protocol can be found in English at:

<http://www.cpc.unc.edu/measure/tools/hiv-aids/place>

The programmatic mapping is based on the PLACE approach: identify the public places (such as hotels, bars, and events) where key populations socialize or meet new sexual partners. These places are potential intervention sites where the individuals most likely to transmit HIV can be accessed. Sites and events are identified by informants in the community. Sites are then mapped and a knowledgeable person at each site is interviewed. Next, key populations working or socializing at sites are interviewed about their sexual behaviors and exposure to HIV prevention at a sample of sites/events. Workers and patrons are also tested for HIV at this time. The full protocol will be carried out in 4 provinces of Angola.

There are five steps in PLACE:

1. Mapping Readiness Assessment, preparation, protocol adaptation in consultation with PLACE technical advisory committee, and district selection
2. Community informant surveys ☐
3. Site visits and mapping ☐
4. Patron, worker and key population interviews and HIV, STI and CD4 testing ☐
5. Feedback and data use☐

#### **Step 1: Mapping Readiness Assessment, preparation and protocol adaptation**

As described above, Individual and/or focus group interviews will be conducted with members of key populations and service delivery organizations to develop a typology of sites where key populations can be reached as well as a typology of the major sub-groups within each key population. The guiding principle will be to identify site and group typology that can be used to inform the provision of services.

In addition, formative interviews will be used to adapt the protocol to the Angolan context, including obtaining appropriate terminology, formats for data collection, training materials, and protocol reviews. A Pilot will be implemented first and the protocol revised as needed.

Initial meetings with stakeholders will be used to identify the ideal categories of knowledgeable informants for the Community Informants survey (Step 2). Given these objectives, the inception meeting will be vital for

planning the survey as well as engaging the stakeholders about the role of programmatic mapping in HIV prevention at the district level. Participation at this meeting will be invited from technical, political and civil society groups that have potential roles in HIV prevention programs.

By the end of each meeting, provincial stakeholders will have a shared awareness of the role of programmatic mapping in the district HIV prevention, as well as guiding survey activities within the urban and rural areas and ideal categories of informants.

### ***Step 2: Community Informant Interviews***

Approximately 500 brief 10-20 minute anonymous Community Informant interviews will be conducted with persons knowledgeable about the community to identify the names of venues and events where people go to meet new sexual partners and where key populations can be reached.

The brief interviews will be conducted to identify venues and events where people meet new sexual partners. Respondents will be asked specifically about places where sex workers and men who have sex with men and transgender women go to meet partners or socialize. The respondents will be selected by interviewers based on their knowledge of the community. Trained interviewers will ask these community informants to identify venues and events where people meet new sexual partners, including sex workers, MSM and transgender women using Form A (see Appendix 2).

A list of venues and events named by community informants will be compiled for use in the second phase of data collection.

The informants will be sought from the categories of informants in the PLACE protocol and unique additional groups identified from the district inception workshops. Efforts will be made within each sampled area to ensure broad representation of the different categories of knowledgeable community informants. Bar managers, taxi drivers, police, security guards, cleaning women, street cleaners, market sellers, sex workers, STI clinic patients, health workers, truckers, college students, and street sellers have proven to be knowledgeable informants in other PLACE studies. Networks of MSM will also be contacted as informants. Recruitment will occur wherever the target types of informants can be found.

Prospective community informants will be approached by interviewers to voluntarily participate in the survey. They will be asked a few questions about their own characteristics and asked to identify venues or events where people go to meet new sexual partners. Specific questions will be asked about MSM venues and sex worker venues. Venues may include places such as bars and restaurants, streets, parks and public events.

Data collection form "Form A" (Appendix 2) is used in this step, and is used to:

- Collect a minimal amount of characteristics about the informant
- Lists the sites/venues identified by the informant and obtains additional information about each site.

Interviewers will be trained in administering community informant interviews during a two-day training. Also during this first training, interviewers will be trained in the PLACE method in general, ethical considerations of research, the importance of confidentiality during the study, and general interviewing techniques. The survey team will be trained to seek out the different informants and interview them in the local language. Translation

of the PLACE tools to the local language will be done at the training workshop to ensure that the appropriate language is used for interview. Due to the multi-lingual nature of most provinces, efforts will be made to have the tool translated into 2-3 languages appropriate for each province. Province-based interviewers will help in anticipating and interpreting the names and location of sites and venues provided by the informants.

#### *Recruitment of Community Informants*

The implementation team will brainstorm a list of the types of people likely to be knowledgeable about venues and set a target number for each type of informant to be named. Setting a target number for each type of informant helps to ensure all types of venues will be named. Bar managers, taxi drivers, police, security guards, cleaning women, street cleaners, market sellers, sex workers, STI clinic patients, health workers, truckers, college students, and street sellers have proven to be knowledgeable informants. Networks of sex workers, MSM and transgender women will also be contacted as informants. Recruitment will occur wherever the target types of informants can be found.

#### *Ethical Considerations for Community Informant Interviews*

Because community informants are only asked to name venues and events in the community and not to report information about their personal behavior, there is no risk involved in this phase of data collection. No personal identifying information is collected.

#### *Consent Process for Community Informant Interviews*

Interviewers will explain to **community informants** the purpose of the study, type of questions asked, and that no identifying information will be collected from them. Community informants will not require formal consent as the data collected from these informants is unrelated to their personal characteristics and is centered on the PPA and/or venue of interest. Community informants will receive a fact sheet about the study with contact number for the local and UNC researchers. They are asked their age in order to confirm eligibility (age 18 or older are eligible). Once eligibility is determined, the interviewer will read a short description of the study and the type of questions that will be asked.

*“Hello. My name is \_\_\_\_\_ and I am working with Tchikos/the National Institute against HIV/AIDS on a study that will improve HIV prevention programs here. I would like to ask you some questions about where people go to meet new sexual partners around here. I can offer you this Fact Sheet that has more information about the study.”*

The interviewer will offer the respondent a Fact Sheet (see appendix) that contains information about the study, including contact information within Angola in case questions arrive after the interview. Next, the interviewer asks if they are willing to participate. If they are willing, the interview begins.

### ***Step 3: Venue Visits and Mapping***

In this step, trained interviewers visit venues reported by community informants to verify the existence of the sites. Interviewers visit their assigned venues, identify a person knowledgeable about each venue (ideally someone from a key population), and then request an interview.

Sex workers, MSM and transgender women community informants will be asked to name the places where key populations receive services including NGOs. Venue visits will include visits to all organizations providing services to sex workers, MSM and transgender women.

Interviewers will be trained in the questionnaire to be used for interviewing a venue representative, as well as in using a GPS device to measure the latitude and longitude of each venue (see Appendix 3).

Internet sites will be visited as well. Efforts will be made to assess the number of people registered at the website and whether or not people registered at the website visit the public sites identified by the community informants. Additional venues and events will be obtained from information obtained on the internet sites. Site visits will be conducted at these new sites as well.

Information collected from venue visit interviews will be used to describe areas where there is risky behavior and to inform prevention programs. The list of venues in operation will be used as a sampling frame for the next phase of data collection, interviews with patrons and workers of venues. Maps will be created using the data to show the geographic distribution of venues and the coverage of prevention programs. Maps can also indicate the location of priority venues for interventions.

#### *Recruitment of Venue Informants*

Each pair of interviewers visits their assigned venues, identifies a person knowledgeable about each venue, and then requests an interview. The knowledgeable person at a venue may not be a manager or owner of that venue. At places like taxi stands, street corners, or parks, these interviews are not conducted with people in a position of leadership over the location. In such situations, the interviewer pair chooses a person who is likely to be familiar with the venue, but is not a manager, owner, or in a position of leadership. For example, a food vendor who regularly sets up near a city park could be approached for an interview about the park. While not in a position of responsibility for the park, this person is likely to know about the types of people that visit there. The field coordinator can be consulted by the interviewers for advice before going to the venue, if necessary.

Site representatives will be asked to participate in an interview about the site that will last 20 to 30 minutes. The questions asked include questions about the type of people who come to the venue, activities at the venue, whether people meet new sexual partners at the venue, and whether the respondent believes it would be feasible to have an HIV prevention activity at the venue sometime in the future. The interviewer is not asking for commitment to an onsite program, but an indication of feasibility. Commitment to an onsite program cannot be provided in any case by many of the respondents, as they will be people without any management responsibility for a venue.

There is one questionnaire used in this step (Appendix 3):

- Form B: Site/Event Verification Questionnaire – obtains characteristics of the site or event, including number and type of patrons, activities onsite, and HIV prevention coverage onsite; one form is completed for each site/event.

Responses to the questionnaire will be recorded on a smartphone. Each site and event visited will also be geo-located using the smartphone.

GPS coordinates of each venue are also obtained so that the geographic distribution of venues can be displayed on a map.

